This protocol is for two RCTs examining the effectiveness of two interventions for staff working in the NHS: (1) MBCT-L and (2) CBT-based stress management. Staff will select one of these two interventions and then will be randomly assigned to either the intervention arm or to the wait-list arm within their preferred choice. Our intention in offering staff a choice between these two interventions is to increase accessibility and choice, acknowledging that no one intervention is likely to meet the needs of all staff.

Given the existing evidence for these interventions is predominantly in stress-reduction, the primary hypothesis is that both interventions will be more effective than the wait-list at reducing stress post-intervention. Secondary hypotheses are that both interventions will be more effective than the wait-list post-intervention in: (1) reducing sickness absence; (2) improving compassion for others; (3) reducing anxiety symptoms; (4) reducing depression symptoms; (5) reducing work-related burnout; (6) improving compassion for self; (7) improving wellbeing; (8) reducing presenteeism and (9) improving mindfulness (in MBCT-L participants only). We also plan to explore participants’ experiences of their chosen intervention using thematic analysis of semi-structured interviews.

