## Methods/design

### Design and sample size

This protocol is for a study of two superiority RCTs with participant preference between the two interventions with 1:1 allocation to either intervention or wait-list within the preferred choice. The randomisation procedure will be web-based and automated; the allocation sequence will be generated and participants randomised using block randomisation by Qualtrics (www.qualtrics.com), the online survey software. Members of the research team involved in the day-to-day management of the study will be blind to block size. Assessments will be completed online by participants at baseline and post-intervention, independent from members of the research team, to reduce risk of bias associated with researcher-administered assessments.

Sample size calculations were conducted using G*Power [13]. The study aims to have 140 participants giving complete data sets at baseline and post-intervention within each part of the study (i.e. aiming for 140 MBCT-L and 140 CBT study completers). Given the pressures on staff time and the online data collection method, it is conservatively assumed that 40% of participants will fail to complete measures post-intervention. This means that we aim to recruit 234 participants into each part of the study.

Sample size calculations are based on an estimated medium between-group effect on post-intervention stress outcomes (Cohen’s *d* = .50) between the intervention and wait-list arms with 90% power and *p* = .05. For MBCT-L, the estimated medium effect size is based on between-group post-intervention effects on stress reported in previous trials of MBIs for healthcare staff [9, 12, 14]. For the CBT stress-management workshop it was not possible to estimate the effect directly based on published trials as previous research has evaluated CBT stress-management interventions running over several sessions. We therefore assume that the effect size will be smaller in the current study than the large effect reported in a meta-analysis of multiple-session CBT stress-management interventions in the workplace [34] and therefore estimate a medium effect size.

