### Planned data analysis

The intention in providing two interventions is to increase choice and accessibility. The intention is not to compare the effectiveness of the CBT intervention directly with the MBCT-L intervention and any such comparison would be problematic given the potential for selection bias (i.e. participants preferring MBCT-L may differ in a number of ways from participants preferring the CBT workshop). Intervention preference will be reported as the number and percentage of participants choosing each intervention type; however we would urge caution when interpreting these data as participant preferences may be driven by practicalities (e.g. location and dates of available courses) as much as by intervention preference.

Between-group differences at baseline on key demographic variables (age, gender, ethnicity, NHS trust, pay band and years working in the trust) and all outcome measures will be reported for each study. Findings will be reported for both intention-to-treat and per-protocol analyses. Hypotheses will be tested using mixed analysis of variance (ANOVA) for each intervention separately, with time (baseline, post-intervention) as the within-group variable and intervention arm (intervention, wait-list) as the between-group variable. Post-intervention between-group effect sizes (Cohen’s *d*) and 95% confidence intervals will be reported. Interaction effects will be followed up with within-group *t* tests, with Cohen’s *d* effect sizes and accompanying 95% confidence intervals for within-group change.

Qualitative data will be transcribed and thematic analysis will be performed in accordance with the Braun and Clarke [7] protocol. This will involve the researcher leading on the qualitative aspect of the study reading and re-reading transcripts, allocating codes to single units of meaning within each transcript, identifying sub-themes representing lower-order categories of meaning across participants (within CBT/MBCT-L separately) and finally identifying higher-order themes and the relationship between themes and sub-themes (for CBT/MBCT-L separately). This will be conducted under supervision from the lead author. Credibility will be checked through supervision and will be indicated through providing comprehensive extracts from participants to illustrate each theme and sub-theme.

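### The planned test is on change from baseline, but the only between-arm effect size and 95% CI specified is a post-intervention Cohen's d with no stated baseline adjustment, so the interval does not belong to the p value and precision is lost

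*Protocol article*

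**What the plan says.** All of the relevant text is in the protocol article.

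- **Test** (Planned data analysis): "Hypotheses will be tested using mixed analysis of variance (ANOVA) for each intervention separately, with time (baseline, post-intervention) as the within-group variable". The randomised arm is the other factor in this model.
- **Follow-up** (same section): "Interaction effects will be followed up with within-group" t tests, with Cohen's d and intervals for within-group change. This marks the time-by-arm interaction as the decisive term.
- **Between-arm estimate** (same section): "Post-intervention between-group effect sizes" as Cohen's d, with 95% confidence intervals. No baseline covariate, adjusted mean or difference in change is mentioned as an estimate.
- **Hypothesis** (Background): "both interventions will be more effective than the wait-list at reducing stress post-intervention".
- **Sample size** (Design and sample size): "Sample size calculations are based on an estimated medium between-group effect on post-intervention stress outcomes", with d = 0.50 "between the intervention and wait-list arms with 90% power and" p = .05. The target is 140 completers per trial, allowing for 40% loss, with "1:1 allocation to either intervention or wait-list within the preferred choice".

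Baseline scores are collected on every self-report scale (Measures, end of the engagement subsection).

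**The concern.** A reader expects the effect estimate, its interval and the p value to describe one contrast. Here the p value concerns the between-arm difference in change, while the interval concerns the between-arm difference at the second assessment. The quantity tested has no interval, and the quantity with an interval is not the one tested.

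A report could then show a significant interaction beside an interval for d that includes zero, or the reverse. The baseline score, which every participant supplies before randomisation, is also left out of the only between-arm estimate. That makes the interval wider than the trial's own data allow.

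**Working it through.** **Inputs.** From the document: 140 completers per trial at 1:1, so 70 per arm; d = 0.50; 90% power; p = .05; 40% loss. Assumed, because the document does not give it: baseline-to-post correlation r from 0.3 to 0.8. Also assumed: normal scores and equal SD (set to 1) at both times. A true effect of 0.30 is added as a sensitivity case. The article says the CBT workshop effect could not be estimated directly from published trials.

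**The plan's own figure.** A two-sample t test on post-intervention scores with d = 0.50, 90% power and one-sided 5% needs 69.2 per arm. That rounds to 70 per arm, or 140, and 140 / 0.60 = 233.3 gives 234. Both stated figures reproduce, so the sizing matches a comparison of post scores. (Two-sided 5% would need 172 completers. The article does not state sidedness; that is a separate matter.)

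**Two different estimators.** With two time points, the interaction F equals the square of the t statistic on change scores. Let the true effect be τ and the chance baseline difference between arms be δ. Given δ:

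- post-score difference: expected value τ + rδ
- change-score difference: expected value τ − (1 − r)δ
- baseline-adjusted difference (ANCOVA): expected value τ

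Averaged over randomisation, δ is zero, so all three target τ. In any one trial the first two differ by exactly the observed baseline difference. The SD of δ is √(2/70) = 0.169, and it exceeds 0.2 SD in either direction in about 24% of trials. At r = 0.5, a 0.2 SD imbalance moves the expected post-score difference by 0.5 × 0.2 = 0.1 SD.

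**Interval half-widths** in SD units at 70 per arm, with t = 1.977:

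- post: 1.977 × √(2/70) = 0.334
- change: multiply by √(2(1 − r))
- ANCOVA: multiply by √(1 − r²)

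| r | post | change | ANCOVA |
|---|---|---|---|
| 0.3 | 0.334 | 0.395 | 0.319 |
| 0.5 | 0.334 | 0.334 | 0.289 |
| 0.6 | 0.334 | 0.299 | 0.267 |
| 0.7 | 0.334 | 0.259 | 0.239 |
| 0.8 | 0.334 | 0.211 | 0.201 |

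For example, take r = 0.7, an observed difference of 0.30 SD and no baseline imbalance. The post-score interval is 0.30 ± 0.334, or −0.03 to 0.63. The interval belonging to the interaction test is 0.30 ± 0.259, or 0.04 to 0.56. The test is significant and the reported interval includes zero.

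**Frequency of disagreement.** 20,000 simulated trials per setting, comparing the two-sided 5% t test on post scores (equivalent to whether the interval for d includes zero) with the t test on change:

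| r | no effect | d = 0.30 | d = 0.50 | at d = 0.50: change significant, post not | at d = 0.50: post significant, change not |
|---|---|---|---|---|---|
| 0.3 | 7.3% | 29.7% | 24.2% | 5.2% | 19.0% |
| 0.5 | 8.2% | 33.3% | 19.5% | 9.9% | 9.6% |
| 0.6 | 8.5% | 35.9% | 18.0% | 12.6% | 5.4% |
| 0.7 | 8.3% | 39.6% | 17.1% | 15.4% | 1.7% |
| 0.8 | 9.2% | 47.4% | 16.4% | 16.2% | 0.2% |

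Repeat runs move these totals by about one percentage point.

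**Power**, two-sided 5%, d = 0.50, 70 per arm: post scores 0.84 at any r; change 0.70, 0.84, 0.91, 0.97 and 1.00 for r = 0.3, 0.5, 0.6, 0.7 and 0.8; ANCOVA 0.87, 0.92, 0.96, 0.98 and 1.00.

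**The case against.** The best defence is that the post-intervention contrast is the protocol's own target. The hypothesis is worded that way and the sample size uses that d, so reporting d on the same scale is coherent. Under randomisation with complete data, the post-score and change-score differences estimate the same effect without bias. The test is fixed in advance, and d is to be reported as an effect size, not used as a second test. Baseline differences on all outcome measures will also be reported, so readers can see any imbalance behind d. All of this stands. It limits the fault to mismatch and imprecision, but it does not supply an interval for the contrast that is tested.

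Some stronger readings are tempting and are not supported:

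- **That the reported effect is biased.** It is not in expectation, given randomisation and complete data. The 40% loss is a planning allowance and is not predicted to differ by arm. Adjustment would in any case remove only the part of differential loss that the baseline score explains.
- **That the plan commits to an unadjusted d as its main result.** The article does not say how d is computed, nor that it is the principal finding. No adjustment is stated, and a fuller plan might define one.
- **That the two results will usually conflict.** At the design effect they agree in at least three trials out of four, and with no effect in more than nine out of ten. Many of the disagreements will be one result just crossing the 5% line and the other just missing it.
- **That results in DASS-21 stress points will be absent.** The article does not say that d is the only summary, and a condensed article may leave this out.

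**Conclusion.** The point holds as a mismatch between estimate and test, with avoidable loss of precision. At d = 0.50 with 70 completers per arm, the interval for d and the interaction test disagree at the 5% level in roughly 1 trial in 4 (r = 0.3) to 1 in 6 (r = 0.8). If the true effect were 0.30, the share would be about 30% to 48%; with no effect it is under 10%. The direction depends on r: at low correlation it is mostly the interaction test that misses, and at high correlation mostly the interval for d that includes zero.

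Using the baseline score would cut the half-width from 0.33 SD to 0.29 (r = 0.5) or 0.24 (r = 0.7).

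These figures rest on the assumed correlation, normal scores, equal SDs and complete data. They also rest on reading the interaction as the decisive term and d as computed from post scores alone, which is the natural reading of the analysis section. The change is worth making, but the trial is not invalid without it.

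**What to change.** In Planned data analysis, replace the mixed ANOVA as the primary test with one baseline-adjusted model fitted separately in each trial. This can be ANCOVA on the post-intervention score with the baseline score as covariate, or an equivalent mixed model with a common baseline mean for the two arms. Take the p value, the adjusted mean difference and its 95% confidence interval from that model, so that they agree by construction. For stress, give the difference in DASS-21 stress points. If a standardised effect is wanted, divide the adjusted difference and both limits by the baseline SD pooled over the two arms. Treat the other self-report scales in the same way.

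A reporting edit alone would not be enough, because the mixed ANOVA interaction yields a difference in change and not a baseline-adjusted difference.

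The cost is a sentence or two and no extra data. The one real downside is that the named primary test changes, so the amendment should be recorded as such. Under the assumptions above, the adjusted model has at least the power of either the post-score or the change-score test at every correlation examined.

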### Dissemination

Findings will be written up for submission for publication in a peer-reviewed journal as 4 papers: (1) reporting on the quantitative findings from the RCT comparing MBCT-L with wait-list; (2) reporting on the quantitative findings from the RCT comparing the CBT-based stress management intervention with wait-list; (3) reporting on the qualitative findings of participating in MBCT-L and (4) reporting on the qualitative findings of participating in the CBT-based stress management intervention. A lay report of findings will be produced for dissemination to participants and other NHS Trust staff.

## Discussion

When compared to other professions, healthcare staff experience particularly high levels of work-related stress and sickness absence [1, 30, 31], with higher levels of stress associated with compromised patient care and safety [18]. Psychological approaches based on psychological theory of stress [25, 26] provide one solution. Evidence for reducing work-related stress is strongest for CBT stress-management [21] and mindfulness-based interventions [41]. However, effects on objective indicators of stress (such as sickness absence) and on factors associated with patient care (such as compassion for others) is largely unexplored. In addition, potential benefits of brief CBT-based stress management courses and of MBCT-L on healthcare staff levels of staff are unknown.

This is a protocol for two separate RCTs with participant preference examining the effects of two interventions, each compared to wait-list, for NHS staff. The first of these is a 1-day CBT stress-management workshop and the second is an 8-session MBCT for Life (MBCT-L) course. The primary outcome is stress, as this is the outcome with the greatest evidence of effects. Secondary outcomes include sickness absence, compassion for others, depressive symptoms, anxiety symptoms, compassion for self, work-related burnout, presenteeism and mindfulness (in MBCT-L participants). Effects on sickness absence would be of particular interest to healthcare employers and would provide an economic incentive to widen access to these interventions. Effects on compassion for others would suggest that benefits to staff might extend to improved patient care and this would lead to further research examining the effects of these interventions for staff on outcomes for their patients. Effects on wellbeing are also important to measure. Whilst the primary outcome in this study is stress, we are interested not only in the potential of the interventions to reduce stress and mental health symptoms, but also of the potential to enhance wellbeing and compassion for self and others. This focus is particularly highlighted in MBIs in the workplace [15] and in MBCT-L, with its emphasis on cultivating appreciation and gratitude [5].

A limitation of the design is that it will not be possible to directly compare outcomes between the two interventions as participants are not randomised between intervention types. A direct comparison of the two interventions could be explored in future trials, depending on the outcomes of the current study. Another limitation is that reasons for sickness absence will not be recorded in order to respect participants’ confidentiality. It is also possible that staff may be reluctant to disclose mental health reasons for sickness absence due to concerns about stigma, and that a physical health reason may be given instead. If the interventions have a beneficial effect on sickness absence due to poor mental health this should be reflected in an overall effect on sickness absence. There is also an important note of caution in relation to the interventions being evaluated. Providing psychologically informed interventions to healthcare staff as a means of reducing work-related stress could contribute to a culture whereby staff members are seen as solely responsible for managing their stress, absolving healthcare organisations from responsibility to provide supportive workplaces that do not place excessive demands on their staff. Individually targeted interventions such as CBT stress-management workshops and MBCT-L can be part of a solution to reducing work-related stress in the healthcare workplace. However, we suggest that this should occur in the context of organisational-level interventions to minimise stress, as these may play an additional important role in reducing stress in healthcare workplaces [32]. Within supportive healthcare organisations, our CBT stress-management workshop and MBCT-L have potential to provide staff with the skills to recognise signs of stress in themselves and the skills to act early to prevent stress from escalating, and thereby empowering staff to make choices about how they respond in stressful healthcare workplace settings.

## Trial status

At the time of manuscript submission, recruitment for this study was ongoing.

### SPIRIT guidelines

Please see Fig. 2 for a copy of the Standard Protocol Items: Recommendations for Interventional Trials (SPIRIT) figure. The SPIRIT checklist can be found as Additional file 1.

**Fig. 2 Fig2:**
[figure not shown]
Schedule of enrolment, interventions, and assessments

## Abbreviations

ANOVA: Analysis of variance
CBT: Cognitive behavioural therapy
DASS-21: Depression, Anxiety, and Stress Scales (short version)
FFMQ-15: Five Facet Mindfulness Questionnaire (15 item version)
FFMQ-39: Five Facet Mindfulness Questionnaire (39 item version)
HR: Human resources
iMTA PCQ: Institute for Medical Technology Assessment Productivity Cost Questionnaire
MBCT: Mindfulness-based cognitive therapy
MBCT-L: Mindfulness-based cognitive therapy for life
MBI: Mindfulness-based intervention
MBI-HSS: Maslach Burnout Inventory – Human Services Survey
NHS: National Health Service
RCT: Randomised controlled trial
SMART: Specific measurable achievable relevant time-limited
SWEMWBS: Short Warwick Edinburgh Mental Wellbeing Scale
